### Sample Size

This is a prospective randomized controlled study. Patients meeting the inclusion and exclusion criteria are randomly divided into two groups, group A (AAF) and group B (EHF). Time to reach full enteral feeding is the primary outcome measure; the same research is unreported at present. According to Raimondi's study (15) and experience in clinical practice, the mean time to full enteral feeding in group A is 23.6 ± 15.6 days, accounting for a 30% disparity, the time to full enteral feeding between the two groups differs by approximately 7.08 days. Hypothesis tests are two-sided with a significance level of 5%, while the statistical power is set at 80%. In this study, Zα = 1.96, Zβ = 0.84, σ represents standard deviation, δ represents the difference between the mean values in the two groups, and the formula for calculating sample size is as follows:

$$\begin{array}{l} n=\frac{{\left(Z_{\alpha }+Z_{\beta }\right)}^{2}*2\sigma^{2}}{\delta^{2}} \end{array}$$

After calculation, a sample size of 76 per group is required, accounting for a 20% miss rate. Ninety-five patients per group need to be included, and the planned sample size of this study is at least 190 patients in total.

### Randomization

Randomization will be performed using the SPSS software package (version 22.0) using a random number generator in a 1:1 ratio. A statistician who is not involved in recruitment and subsequent data analysis will generate the randomization list, and the list will be concealed. After random allocation lists have been generated, the allocation group (AAF or EHF) will be stored in sequentially numbered, sealed, opaque envelopes. These envelopes will be opened by a third-party individual at each study enrolment after baseline measures have been obtained.

The study will be double*-*blinded. A nutritionist who is not directly involved in inpatient care will prepare and label the formula with the participant's randomization number, date, and time of feeding, and then deliver the formula to the nurse caring for the infant. The medical and nursing teams caring for the infants will be unaware of the type of formula used for feeding. The trial statistician will perform data analysis and be kept unaware of treatment group assignment until the results are finalized.

### Feeding Schedule

According to the guideline for nutrition support (19), enteral feeding is started within the first 24 h of life. Human milk is encouraged, and preterm formula is fed when human milk is not available due to the mother's or family's condition. Patients with FI are temporarily fed with AAF (Neocate® Nutricia, London, UK) or EHF (Alfare® Nestle, Netherlands) instead of HM or PF. Nutritional feeds start at 15–20 mL/kg/day and are increased by 20–30 mL/kg/day. The gastric residual volume (GRV) is checked before each feeding. If GRV is ≥ 50% of the previous feeding, then enteral feeding was ceased for 1 h, and patients are reassessed. If GRV is not improved, complete blood count, C-reactive protein (CRP), and abdominal X-rays are performed and assessed. If these results can rule out NEC and severe infection, patients are fed in the same amounts for 2–3 days. Enteral feeding is increased at the same rate until full enteral feeding (150 mL/kg/day) every 3 h is reached. Enteral feedings are withheld: in the presence of bloody or biliary gastric residuals, in cases of abnormal abdominal examination, and/or in cases of abnormal abdominal X-ray. As soon as the residuals, the abdominal examination, and/or X-ray return to normal, feeding is resumed with AAF or EHF at the same speed. Once the patients with FI show clinical improvement, AAF or EHF feeding is discontinued, and the previous feeding, either HM or PF is resumed. When full enteral nutrition is insufficient, all patients receive parenteral nutrition solutions (6), which are gradually decreased with increasing enteral feeding. Other routine treatments for FI are given in the two groups according to the guidelines. Table 3 shows the study formulas. Figure 2 shows the feeding schedule.

**Table 3 T3:** Study formulas.

**Characteristics**	**Study formula**	
	**AAF**	**EHF**
Nutrient density (KJ/100ml)	279	284
Nutrient composition per 100 ml		
Total Protein (g, % calories)	2.0,12%	1.82,11%
Total Carbohydrate (g, % calories)	7.0,42%	7.5,43%
Total Fat (g, % calories)	3.4,46%	3.39,46%
Arachidonic acid (ARA), mg	11.3	8.5
Docosahexaenoic acid (DHA), mg	11.3	8.5
Minerals		
Phosphate (mg/100 ml)	59	46
Calcium (mg/100 ml)	85	68
Iron (mg/100 ml)	1.1	0.7
Osmolarity (mOsm/L)	310	170

**Figure 2 F2:**
[figure not shown]
Feeding schedule.

### Variables Studied

The investigator who is responsible for recruitment will perform all the evaluations and remain blinded to the status of the patients with regard to the intervention throughout the study.

Table 4 shows the demographic variables. The following variables: age, sex, birth weight, birth length, delivery mode, gestational age, multiple gestations, family history, birth history, and history of present condition.

**Table 4 T4:** Demographic variables.

**Variables**	**values**
Age Sex Gestational age Birth weight Delivery mode Multiple gestations Apgar score (1', 5', 10') Maternal health during pregnancy Adverse events at birth	Days Male/Female Weeks g vaginal delivery or cesarean section Yes/no 1-10

### Outcome

#### Primary Outcome

Time (days) to reach full enteral feedings, defined as a daily intake of ≥ 150 mL/Kg/day for 3 days in a row (age at the first day of achieving full enteral feedings as the indicator).

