**Figure 1 F1:**
[figure not shown]
The overall design of the study.

**Table 1 T1:** Data collection schedule.

	**Staff member**	**T1**	**T2**	**T3**	**T4**	**T5**
Symptom of FI	Neonatal physician	**×**				
Informed consent	Research assistant	**×**				
Contact information	Research assistant	**×**				
Sex	Neonatal physician		**×**			
Gestational age	Neonatal physician		**×**			
Mode of delivery	Neonatal physician		**×**			
Apgar score	Neonatal physician		**×**			
Maternal issues	Neonatal physician		**×**			
Weight	Neonatal nurse		**×**			**×**
Gastric residual volume	Neonatal nurse			**×**	**×**	
Abdominal circumference	Neonatal nurse			**×**	**×**	
Length	Neonatal nurse		**×**			**×**
Head circumference	Neonatal nurse		**×**			**×**
Time to reach total enteral nutrition	Neonatal physician					**×**
Duration of abdominal distension	Neonatal physician					**×**
Duration of vomiting	Neonatal physician					**×**
Length of hospital stay	Neonatal physician					**×**
Cost of hospitalization						**×**
Time of parenteral nutrition	Neonatal physician					**×**
Main serum parameters	Neonatal physician			**×**	**×**	
Incidence of adverse events	Neonatal physician					**×**

*T1 screening; T2 baseline evaluation; T3 beginning of intervention; T4 end of intervention; T5 discharge*.

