### Study Population

Table 2 specifies all inclusion and exclusion criteria.

**Table 2 T2:** Inclusion and exclusion criteria.

Inclusion criteria
• Admission between December 2021 and December 2023.
• Gestational age (GA) <32 weeks or birth weight (BW) <1,500 g, appropriate for gestational age, admitted to Department of neonatology, Children's Hospital of Chongqing Medical University within the first 24 h after birth, maximal enteral intake <50 ml/kg/day
• Patients are fed with PF when HM is not available after admission
• Meet the diagnostic criteria of FI. Currently, a clear and universal definition of FI is lacking, FI is defined as follows with reference to relevant literature (5, 16–18): One or two of the criteria below are met: (1) gastric residual volume ≥50% of the previous feeding volume (≥ two times within 24 h), with the presentation of vomiting and/or abdominal distension; (2) feeding plans fail: including feeding withheld or decrease > 6 h, or not increased >24 h (5)
• Parental consent has been obtained
Exclusion criteria
• Perinatal asphyxia: (1) Apgar score of <4 at 5 min; (2) Fetal umbilical artery acidemia: pH <7.00 and/or base deficit worse than or equal to minus 12 mmol/L; (3) A significant peripartum or intrapartum hypoxic-ischemic event (e.g., uterine rupture, placental abruption, cord prolapse, amniotic fluid embolism, fetal exsanguination from a vasa previa or massive feto-maternal hemorrhage, etc.).
• Potential metabolic or chronic disease, congenital abnormality, or any other diseases that may affect feeding ability, normal growth, and development before recruitment
• Patients who need surgical treatment under general anesthesia (ligation of patent ductus arteriosus is excluded) before or on the date of randomization
• Blood pressure is unstable (allowing for dopamine <5 μg/kg/min)
• Ventilator dependence or FiO2 >40% on the date of randomization (allowing for nasal intubation, CPAP, and/ or oxygen mask)
• Grade III or IV intraventricular hemorrhage is diagnosed before or on the date of randomization

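### The primary outcome runs from birth although the formula is allocated only after feeding intolerance is diagnosed, and the planning figure of 23.6 ± 15.6 days has no stated time origin

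*Protocol article*

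**What the plan says.** The Primary Outcome section names the endpoint as "Time (days) to reach full enteral feedings, defined as a daily intake of" at least 150 mL/kg/day on three consecutive days. It then fixes how the time is measured: "age at the first day of achieving full enteral feedings as the indicator". Day zero is therefore birth.

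The rest of the protocol article places allocation later:

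- Table 2 requires admission "within the first 24 h after birth". It describes feeding before entry ("Patients are fed with PF when HM is not available after admission") and requires that infants already "Meet the diagnostic criteria of FI". It also caps maximal enteral intake below 50 mL/kg/day. No upper age at randomisation is given.
- Under Feeding Schedule, "enteral feeding is started within the first 24 h of life" with human milk or preterm formula. The amino acid-based or extensively hydrolysed formula replaces these only in infants with feeding intolerance.
- Under Randomization, envelopes are opened at enrolment, after the baseline measures.
- The Table 1 footnote treats the start of intervention as its own time point, after screening and baseline: "T1 screening; T2 baseline evaluation; T3 beginning of intervention; T4 end of intervention; T5 discharge".

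The Sample Size section takes 23.6 ± 15.6 days for the amino acid group from a cited study and clinical experience, and continues: "accounting for a 30% disparity, the time to full enteral feeding between the two groups differs by approximately 7.08 days". It does not say when that time starts. Statistical Analyses gives a t-test or Mann-Whitney test for continuous outcomes.

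**The concern.** Age at full feeding is the sum of two parts: age at randomisation, and time from randomisation to full feeding. The first part is fixed before the envelope is opened, so the formula can act only on the second. Two consequences follow.

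1. **Precision.** Variation in age at diagnosis enters the outcome, and the stated tests do not remove it. A chance difference between the arms in age at diagnosis also carries over into the observed difference.
2. **Planning.** If 23.6 days is an age, the 30% was taken partly over days before treatment. If it runs from the start of formula, neither the mean nor the SD of 15.6 describes the outcome as defined. In both cases the reader cannot tell whether the 80% power refers to this endpoint.

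**Working it through.** **Inputs from the protocol article.** Mean 23.6 days, SD 15.6, disparity 30%, two-sided 5%, power 80%, Zα = 1.96, Zβ = 0.84 and 20% loss (Sample Size).

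**Input not in the document.** The SD of age at randomisation, called s₀. I take 3, 5 and 7 days as an assumed range and, to begin with, assume that it is independent of the time after randomisation.

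**Step 1: the plan's own figure.**
- Difference: 0.30 × 23.6 = 7.08 days.
- n = (1.96 + 0.84)² × 2 × 15.6² / 7.08² = 76.1, stated as 76 per group.
- 76 / 0.8 = 95 per group, 190 in total.
- Two-sample t-test power at 76 per group: 79%.

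The arithmetic is sound. The open question is which clock the inputs belong to.

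**Step 2: if 15.6 is the SD of age at full feeding.** Counting from randomisation removes s₀, so SD = √(15.6² − s₀²).

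| s₀ | SD from randomisation | Power for 7.08 days, 76 per group |
|---|---|---|
| 3 | 15.3 | 81% |
| 5 | 14.8 | 84% |
| 7 | 13.9 | 88% |

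**Step 3: if 15.6 is the SD after randomisation.** The age-based outcome then has SD = √(15.6² + s₀²).

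| s₀ | SD of age at full feeding | Power for 7.08 days, 76 per group |
|---|---|---|
| 3 | 15.9 | 78% |
| 5 | 16.4 | 75% |
| 7 | 17.1 | 72% |

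**Step 4: which s₀ is plausible.** On the stated schedule (start at 15–20 mL/kg/day, then add 20–30 per day), intake is 35–50 on the second day and 55–80 on the third. An infant advancing normally therefore leaves the range below 50 mL/kg/day within about 2–3 days. Stalled feeds can delay entry, so this is not an age cap, but it makes early entry likely and favours the smaller values of s₀.

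**Step 5: dropping independence.** Let P be the SD of time after randomisation and r its correlation with age at randomisation. The variance of age at full feeding is s₀² + P² + 2·r·s₀·P. This equals P² when r = −s₀/(2P). With s₀ = 5 and P = 15.6, r = −5/31.2 = −0.16. If infants diagnosed later need somewhat less time afterwards, changing the clock gains nothing. With a stronger negative correlation, age is the less variable outcome.

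**Step 6: chance imbalance.** The standard error of the between-group difference in mean age at randomisation is s₀ × √(2/76), which is 0.49, 0.81 and 1.14 days for s₀ = 3, 5 and 7. The target difference is 7.08 days.

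**The case against.** The strongest reply is that nothing here biases the trial. Allocation is randomised and concealed, so earlier days are balanced in expectation and cancel from the mean difference: 7.08 days in age is also 7.08 days from randomisation. Age at full feeding is explicitly defined, easy to interpret clinically and consistent with the stated aim. Any chance imbalance is small (step 6) and is already part of the ordinary standard error. Adjustment for a covariate is commonly left to an analysis plan, which is not shown. All of this stands, so the missing adjustment is not itself a fault, and the point concerns efficiency and clarity of planning.

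A reader might go further and infer that the true planning effect is smaller. With a mean age at randomisation of 5 or 10 days, 30% of the remaining days is 0.3 × 18.6 = 5.6 or 0.3 × 13.6 = 4.1 days. With SD 15.6, power at 76 per group would be 59% or 36%. The documents do not support that conclusion. The protocol uses 30% only to arrive at a planning difference and nowhere says that the formula shortens post-randomisation days by 30%. Mean age at randomisation is not given. If the SD shrank in proportion to the mean on the later clock, power would stay at 79%.

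What the objection does not answer is that the outcome includes days before treatment by a stated rule, and that the planning figure has no stated time origin.

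**Conclusion.** The point holds as a matter of precision and of unclear planning inputs, and it should be fixed. It does not threaten the validity of the primary comparison.

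For an assumed SD of age at randomisation of 3 to 7 days, independent of later time, the choice of clock is worth about 2 to 9 percentage points of power if 15.6 is the SD of age (79% to 81–88%). If 15.6 is the SD after randomisation, it costs about 1 to 7 points (79% to 78–72%). The entry limit on intake makes the low end more plausible. A correlation of about −0.16 at an SD of 5 would remove the gain from changing the clock.

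A reader might infer from this that the trial is underpowered. The documents do not establish that, or even the direction of any error in power, because that depends on the unstated clock of the 23.6 ± 15.6 days. I am confident about the mismatch between the outcome's clock and the time of allocation, but not about its size.

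**What to change.** 1. **Outcome.** Define the primary outcome as days from randomisation (start of study formula, T3) to the first of three consecutive days at ≥150 mL/kg/day, with age at full feeding as a secondary outcome. Alternatively, keep age as primary and adjust for age at randomisation in a linear model. Adjustment protects precision whatever the correlation, because both clocks then give the same residual variance.
2. **Planning figures.** State the time origin of the 23.6 ± 15.6 days, and restate the mean, SD and difference on the clock of the chosen outcome.
3. **Covariate.** Age in days is already listed in Table 4. State that it is age at randomisation.

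The cost is a few sentences and no extra procedure for the infants. A result counted from randomisation is less directly comparable with studies that report age at full feeding, but the secondary outcome covers that.

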#### Secondary Outcome

Duration of vomiting and abdominal distension (a 24-h abdominal circumference increase of ≥1.5 cm).Gastric residual volume (measured by aspirating with a 5-ml syringe before each feeding).Body weight, length, and head circumference during hospitalization.Length of hospital stay (days).Cost of hospitalization.Time (days) of parenteral nutrition.Change of abdomen circumference (measured at a specific time every day).Main serum parameters (blood, liver and kidney function, and electrolytes).Incidence of adverse events.

**Study endpoint**: The day of discharge

**Follow*-*up plan**: No.

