#### Exit Criteria

Death or discharge before total enteral nutrition.Guardian request to withdraw from the study.Sepsis, NEC, use of ventilatory support, or critical illness is not suitable for continuing to participate in the study.

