### Statistical Analyses

The statistical analysis is performed using the SPSS software package, version 22.0. The measurement data obeying the normal distribution are expressed as x ± s, and the *t-*test is used for comparison between groups. Non-normally distributed continuous variables are expressed as median with interquartile range and compared using the Mann-Whitney U test. The enumeration data are expressed by rate (%) and analyzed by the chi-square test or Fisher's exact test. *P* <0.05 is considered a significant statistical difference.

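### Length of stay, hospital cost and parenteral nutrition days are compared as raw totals that death cuts short, with death and serious illness treated only as exits

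*Protocol article*

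**What the plan says.** The Secondary Outcome section of the protocol article lists "Length of hospital stay (days).Cost of hospitalization.Time (days) of parenteral nutrition" without further definition. It sets the study endpoint as "The day of discharge" and plans no follow-up. Table 1 records the three totals, and adverse events, at discharge.

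The Statistical Analyses section gives one rule for all continuous variables. For normally distributed data a t-"test is used for comparison between groups". Otherwise, "Non-normally distributed continuous variables are expressed as median with interquartile range and compared using the Mann-Whitney U test".

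The Exit Criteria include "Death or discharge before total enteral nutrition", and also "Sepsis, NEC, use of ventilatory support, or critical illness is not suitable for continuing to participate in the study". Guardian withdrawal is a further exit. The article does not say whether an infant who exits contributes a total up to that point, is followed to discharge, or is left out. Mortality is not a named outcome; the nearest entry is the incidence of adverse events.

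**The concern.** The article reads lower values of these outcomes as better. Its Background names longer stay and higher cost as consequences of feeding intolerance, and its Discussion suggests that the amino acid-based formula may shorten parenteral nutrition. A plain comparison of totals supports that reading only if a short total means recovery. Death also ends a stay, stops the accrual of cost and stops parenteral nutrition, and neither stated test distinguishes the two.

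Leaving out infants who die or become seriously ill does not solve the problem. It replaces the randomised comparison with one between infants selected by what happened after randomisation. The Discussion itself suggests that formula may affect nosocomial infection, so exit could plausibly depend on the arm.

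The issue is separate from how exits affect the primary outcome. Following exited infants to the end of their stay would restore the randomised groups, but a death on day 10 would then enter as a 10-day stay. A rule for death is still needed. At stake is whether a difference on these three outcomes can be read as a benefit.

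**Working it through.** **The plan's own figure.** The Sample Size section assumes that "the mean time to full enteral feeding in group A is 23.6 ± 15.6 days", a difference of 7.08 days, and the multipliers 1.96 and 0.84:

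n = (1.96 + 0.84)² × 2 × 15.6² / 7.08² = 7.84 × 486.72 / 50.13 = 76.1 per group.

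Allowing for 20% loss, 76 / 0.8 = 95 per group, or 190 in total. The plan's figures reproduce. They concern the primary outcome and are not affected by this point.

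**Route 1: totals run to death.** Suppose survivors in both arms have the same mean stay S, deaths occur on mean day D, and the proportions dying are p₁ and p₂. The mean total in an arm is (1 − p)S + pD, so the arms differ by

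(p₁ − p₂) × (S − D).

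The documents give none of these inputs. The assumed ranges are deaths of 2% versus 5–10% (about 2 versus 5–10 infants of 95), S = 45–60 days and D = 10–20 days.

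- Smallest shift: (0.05 − 0.02) × (45 − 20) = 0.75 days.
- Largest shift: (0.10 − 0.02) × (60 − 10) = 4.0 days.

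In both cases the arm with more deaths has the shorter mean stay although the formulas do not differ among survivors. If D exceeds S, the sign reverses.

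**Effect on the test.** A simulation used 95 infants per arm and the same survivor stay in both arms (lognormal, mean 45, SD 20 days; assumed). It applied the Mann-Whitney test at two-sided 5%, with 3,000 runs per scenario and totals counted to death. The shift is the mean stay in the first-named arm minus that in the second.

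| Deaths by arm | Deaths on days 3–25: shift; rejection rate | Deaths on days 40–80: shift; rejection rate |
|---|---|---|
| 5% vs 5% | −0.1 days; 5% | 0.0 days; 5% |
| 8% vs 2% | −1.9 days; 10% | +0.9 days; 7% |
| 10% vs 5% | −1.5 days; 8% | +0.8 days; 7% |
| 15% vs 5% | −3.1 days; 20% | +1.5 days; 10% |

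The formula agrees. For 8% vs 2% with deaths on average at day 14, 0.06 × (45 − 14) = 1.9 days. The 15% vs 5% row goes beyond the mortality range assumed above.

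**Route 2: deaths dropped.** In the same runs, leaving out infants who died gave shifts between −0.1 and +0.1 days and rejection rates of 4.3–5.1%. That follows from the set-up, in which death was unrelated to how long the infant would otherwise have stayed. If the infants who die or exit are the sicker ones, and exit differs by arm, the remaining groups are no longer comparable. The sample size allows for 0.20 × 95 = 19 losses per arm, enough for such selection to matter. The documents offer no basis for a figure.

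**Which route applies.** The text does not settle it. If the words about total enteral nutrition in the first exit criterion qualify death as well as discharge, a death after full feeding is not an exit on that ground. It is not the stable discharge described under Termination Criteria either. Such an infant could remain in the data with a truncated total while earlier deaths are dropped, so both routes could operate in the same analysis.

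**The case against.** The strongest objection is that the article does not say deaths are counted as short stays. Death is an exit and the sample size allows for 20% loss, which fits leaving exits out. In that case no death enters as a short, cheap stay. This stands. A reader might infer that the plan makes the arm with more deaths look better, or that both ways of handling deaths do so. The documents support neither inference. Late deaths reverse the sign, dropping deaths unrelated to prognosis gives about no bias, and equal mortality gives none. Nor does anything in the documents show that an infant who dies costs less.

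The size also rests entirely on assumptions. Table 2 excludes many of the sickest infants at entry, so mortality may be low and similar in the two arms. That too stands.

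A third objection is that safety is not judged from length of stay, since adverse events are a listed outcome. That limits the harm, but mortality is not named and nothing ties it to the reading of these three totals.

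A fourth is that the handling of deaths in secondary outcomes is commonly left to the full protocol or analysis plan, which are not shown. A rule may exist there. But the article does fix the outcomes, the tests and the exits. Applying them as written gives one of the two problems above, and a rule that cures them has to add to or depart from the stated analysis.

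Finally, an analysis of time to discharge alive would by itself credit infants discharged before full enteral feeding, which the article treats as an exit. This is correct, and the remedy has to allow for it.

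**Conclusion.** The point holds in a limited form. The article specifies simple comparisons of three totals that death truncates and makes death and serious illness exits. It therefore leads either to totals cut short by death or to a comparison of infants selected after randomisation. Neither can safely be read as shorter is better.

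Direction and size are unknown. The 0.75–4.0 days applies only if totals run to death, deaths are early, and mortality is 2% in one arm and 5–10% in the other with a survivor stay of 45–60 days. A claim that the plan will present harm as benefit would go beyond the text. These are secondary outcomes, and the primary outcome and the sample size do not depend on this point. The change is still worth making, because a better analysis is available from outcomes the trial already collects.

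**What to change.** 1. Keep every randomised infant in the analyses of these three outcomes, using hospital data to discharge or death whatever the exit reason. The exception is an infant whose guardian withdraws consent to use of the data.
2. For length of stay and parenteral nutrition days, choose one of two methods in advance:
   - Rank deaths as worse than the longest observed value in the Mann-Whitney test already planned. The test then has to be used regardless of normality, because a worst rank has no value in days for a t-test.
   - Analyse time to discharge alive and time to stopping parenteral nutrition alive, with death as a competing event.
3. Under either method, do not count discharge before total enteral nutrition as a favourable event. For example, treat it as a further competing event, or rank it behind all infants discharged after reaching full feeding.
4. Report cost for all randomised infants, including deaths and exits, next to the numbers of deaths and exits by arm.

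The cost is a few sentences of analysis text and a little programming. Stay, cost and parenteral nutrition are already collected and should be obtainable from the hospital record for infants who exit. The small downside is that a worst-rank or cumulative incidence result is less familiar to readers than a difference in mean days.
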